## Abstract

**Background:**

Telehealth services based on at-home monitoring of vital signs and the administration of clinical questionnaires are being increasingly used to manage chronic disease in the community, but few statistically robust studies are available in Australia to evaluate a wide range of health and socio-economic outcomes. The objectives of this study are to use robust statistical methods to research the impact of at home telemonitoring on health care outcomes, acceptability of telemonitoring to patients, carers and clinicians and to identify workplace cultural factors and capacity for organisational change management that will impact on large scale national deployment of telehealth services. Additionally, to develop advanced modelling and data analytics tools to risk stratify patients on a daily basis to automatically identify exacerbations of their chronic conditions.

**Methods/Design:**

A clinical trial is proposed at five locations in five states and territories along the Eastern Seaboard of Australia. Each site will have 25 Test patients and 50 case matched control patients. All participants will be selected based on clinical criteria of at least two hospitalisations in the previous year or four or more admissions over the last five years for a range of one or more chronic conditions. Control patients are matched according to age, sex, major diagnosis and their Socio-Economic Indexes for Areas (SEIFA). The Trial Design is an Intervention control study based on the Before-After-Control-Impact (BACI) design.

**Discussion:**

Our preliminary data indicates that most outcome variables before and after the intervention are not stationary, and accordingly we model this behaviour using linear mixed-effects (lme) models which can flexibly model within-group correlation often present in longitudinal data with repeated measures. We expect reduced incidence of unscheduled hospitalisation as well as improvement in the management of chronically ill patients, leading to better and more cost effective care. Advanced data analytics together with clinical decision support will allow telehealth to be deployed in very large numbers nationally without placing an excessive workload on the monitoring facility or the patient's own clinicians.

**Trial registration:**

Registered with Australian New Zealand Clinical Trial Registry on 1^st^ April 2013. Trial ID: ACTRN12613000635763

## Background

In industrialized nations approximately 70-78% of healthcare budgets are spent on the management of chronic disease or its exacerbation [1–3] and as the population ages the burden of chronic disease increases and places healthcare budgets under increasing strain.

A strong primary health care system has been acknowledged as critical to the sustainability of health care systems both in developing and industrialised nations and it has emerged as a recurrent theme in recent years [4–6]. The management of chronic disease, much of which could occur in home and community settings, often unnecessarily burdens hospital-centric public health system. As a consequence policy makers and health service managers seek innovations that deliver the same or improved health services using proportionately fewer resources.

Telehealth services have been demonstrated internationally to be one such innovation [7, 8], but there are low levels of evidence from Australian studies [9]. This study will evaluate whether the introduction of in-home telemonitoring services to the management of chronic disease in the community reduces patient use of the health system and improves healthcare outcomes and their quality of life.

We will also explore the extent to which real-time risk stratification of these patients is of value to health professionals and the issues and challenges in deploying telemonitoring services in the community.

Telehealth and telecare technologies and services for the management of chronic disease at home and in the community have been of intense interest in developed western economies because of unprecedented growth rates of the aged population and increasing morbidity as population ages. These factors place unsustainable stress on established health care services, and will result in increasing deficits in clinical human resources, expanding disease management programs and patient demand for greater self-management.

Telehealth services, delivered through home tele-monitoring, have been demonstrated to deliver cost effective, timely and improved access to quality care [7, 9–12]. They also reduce social dislocation and enhance the quality of life and the sustainability of these communities by allowing chronically ill and aged members to stay in their homes and communities longer.

However experience in Australia with the deployment of Telehealth services is extremely limited [13], with most deployments of small scale and lacking detailed analysis of key success factors such as:

 Health care outcomes Health economic benefits Impact on clinical work force availability and deployment Human factors (acceptability, usability by patients, carers, nurses, GPs and administrators) Workplace culture Capacity for organisational change management and business processes

The development of a robust business case and business models for large scale commercial deployment of Telehealth services, based on reliable socio-economic evidence, is therefore essential if these services are to be deployed nationally to mitigate the escalating costs of health service delivery and the increasing deficit in clinical work force.

This trial will seeks to create a robust evidence base for these key success factors and demonstrate an effective and scalable model for an internet-enabled Telehealth services in Australia. Armed with the insights provided by this evidence base, policy makers may have much of the data they require to implement funding models and create a sustainable Telehealth services sector in Australia.

Despite large national investments in health IT, very little policy work has been undertaken in Australia in deploying Telehealth in the home as a solution to the increasing demands and costs of managing chronic disease. In contrast in the UK, the first report from the Department of Health (DH) on this subject was published in 2000 [14] and many others have followed since [15–17]. The DH’s Preventative Technology Grant (PTG) from 2006–08 provided £80 M to local authorities and their partners for investment in assistive technology [18] and most recently £31 m of funding for a Whole System Demonstrator (WSD) program which had Telehealth as an integral part for the management of long-term conditions [11, 19].

The Litan report [7] provides a comprehensive review of the international evidence that Telehealth services for the management of chronic disease can reduce admission to Accident and Emergency (A&E) from between 20-60%. In one report quoted, Strategic Healthcare Programs, LLC (2004), Physiological monitoring of Heart and lung disease and diabetes reduced A&E visits by 49% for Congestive Heart Failure (CHF) patients, 66% for Chronic Obstructive Pulmonary Disease (COPD) patients, and 83% for diabetes patients.

Most recently the Whole System Demonstrator [11] Headline Findings released by the UK Department of Health in December 2011, demonstrated;

 15% reduction in A&E Visits 20% reduction in emergency admissions 14% reduction in elective admissions 14% reduction in bed days 8% reduction in tariff costs and 45% reduction in mortality rates

This was the largest randomised control trial of telehealth and telecare in the world, involving 6191 patients and 238 GP practices across three sites, Newham, Kent and Cornwall. Three thousand and thirty people with one of three conditions (diabetes, heart failure and COPD) were included in the telehealth trial [19].

The most large scale example of Telehealth use is in the US by the Veterans Health Administration (VHA). VHA mainstreams clinical care within its Coordinated Care and Home Telehealth (CCHT) project [12]. Routine analysis of data obtained for quality and performance purposes from a cohort of 17,025 CCHT patients shows the benefits of a 25% reduction in numbers of bed days of care, 19% reduction in numbers of hospital admissions, and mean satisfaction score rating of 86% after enrolment into the program. VHA’s experience is that an enterprise-wide home telehealth implementation is an appropriate and cost-effective way of managing chronic care patients in both urban and rural settings.

Most recently [20] the US Department of Veterans Affairs announced that 690,000 US veterans received care in the 2014 fiscal year via telehealth, with 2 million telehealth visits scheduled. That means that 12 percent of all veterans enrolled in VA programs received telehealth care of some kind in 2014.

### Aims and objectives

This study was designed with the aim of demonstrating how telehealth services for chronic disease management in the community can be deployed nationally in Australia in a range of hospital and community settings and to develop advanced modelling and data analytics tools to risk stratify patients on a daily basis to automatically identify exacerbations of their chronic conditions.

The following research questions will be addressed;

 Effect of telemonitoring on health service utilisation Unscheduled visits to hospital, visits to GPs and Nurse visitsCost and frequency of consultations, laboratory tests and other clinical procedures Effect of telemonitoring on patients outcomes Quality of life, progression of chronic condition, wellbeing, medication adherence Service implementation and deployment Existing model of care, service design, adoption and appropriation User experience and service implementation Satisfaction, useability, acceptance, workload, anxiety and strain among study participants including health professionals, administrators, patients and carers

 Service implementation issues How the new home monitoring service is implemented at each site. What impact has this had on the process and outcomes of normal care delivery?How are existing service practices evolving as a result of the new service?What can be learnt from different implementation approaches? Cost effectiveness analysis Analysis of reductions/increases in costs borne by patients as a result of telehealthAnalysis of reductions/increases in costs borne by the commonwealth and on-the-ground service providers for patients as a result of the deployment of telehealth services

The Project Objectives are to:

 Demonstrate and document how telehealth services can be successfully deployed across Australia, by piloting services in five different settings across five states with a range of health service provider’s, including Local Health Districts, Medicare Locals and not for profit community organisations. This will be demonstrated by deploying and demonstrating the operation of Telehealth monitoring in a multi-site multi-state case matched control trial (Before-After-Control-Impact (BACI) design) of chronically ill patients living in their own homes in the community. This has never previously been attempted in Australia. Provide the clinical and health economic evidence on how Telehealth services can be scaled up nationally to provide an alternative cost effective health service for the management of chronic disease in the community. Provide evidence that at home telemonitoring has the potential to reduce unscheduled admissions to Accident and Emergency (A&E) compared to the control group. Provide evidence for an impact on hospital admissions, mortality, clinical events and symptoms and improvements in functional measures and patients' and carers’ experiences with care. Evaluate health economic benefits Evaluate impact on clinical work force availability and deployment Evaluate impact of human factors (acceptability, usability by patients, carers, nurses, GPs and administrators, impact on workplace culture) Evaluate impact of workplace culture Evaluate impact of organisational change management and business processes Develop a new evidence based data analytical technique for the risk stratification of patients’ health status daily and demonstrate that this facilitates the management of large numbers of patients by orchestrating an optimal and timely allocation of resources to avoid unnecessary hospitalisation

For each of the above objectives, operation of the trial at five different sites representing a range of different models for the management of chronic disease in the community will allow the identification and analysis of site specific differences in workplace culture, organisational change management and staff and management capabilities that contribute to differences in measured health, social and economic outcomes.

## Methods/Design

Immediately following granting of funds for the project in December 2013, Ethics Approval was sought and granted by the CSIRO CAFHS Human Research Ethics Committee, on the 25^th^ March 2013 (approval # 13/04). Subsequently, ethics approval was also obtained from health authorities at each of the test sites as well as from the Commonwealth Department of Health and Ageing and the Department of Human Services. The latter two were necessary in order to be granted access to national patient data stored in the Medicare MBS and PBS archives.

The trial sites are located over widely dispersed regions of the Eastern Seaboard of Australia as shown in Figure 1. They were selected on the basis of three criteria, (i) early participation in the rollout of the National Broadband Network, (ii) geographical location and demographics and (iii) variations in models of care used to manage Chronic disease to be generally representative of the variety of models of care for the management of chronic disease existing in Australia.

**Figure 1 Fig1:**
[figure not shown]
**Trial sites along Eastern seaboard of Australia and in Tasmania.**

### Organisation and management

Establishing an appropriate Governance model for managing such a complex project is critical in order to comply with the requirements of the National Statement on Ethical Conduct in Human Research (2007) [21], the specific requirements of multiple Human Research Ethics Committees and the statutory requirements of the Therapeutic Goods Administration regarding the use of medical devices for monitoring health status.

The Organisational structure shown below in Figure 2 was established in April 2013. Clinical groups meet on a weekly basis and are chaired by the Project Manager or the Clinical Trial Coordinator. The four research teams also meet weekly to monitor progress against project milestones. The Project Management Committee meets monthly to monitor and review progress of the project against its stated aims and objectives. The Management Committee is Chaired by the Project Director and includes representatives from each site as well as two clinicians, one representing the interests of General Practice and the other, Chairing the Adverse Events and Death Review committee which meets whenever necessary.

**Figure 2 Fig2:**
[figure not shown]
**Project organisation and management structure.** CTC – Clinical Trial Coordinator. PO –Project Officer and CCC – Clinical Care Coordinator at each trial site.

### Selection of trial participants

Since random selection of patients was not possible because of small sample sizes and the initial requirement that Test patients be selected from areas connected to the NBN, a **B**efore **A**fter Control **I**ntervention (BACI) design [22] was adopted that foregoes assumptions of normality. The BACI paired samples design provides greater control over confounding variables, increases the power of the study and improves the chances of finding a significant result with a smaller number of samples if the impact is relatively small.

The research protocol requires the recruitment of 75 participants at each of the five sites to achieve a total sample size of 375. Of these 125 are Test patients and 250 are Control patients. At each site 25 participants are allocated to the intervention, with 50 remaining control participants receiving normal care as per their site’s existing model of care.

Eligible candidates are identified primarily by searching the local hospital patient administration system (PAS) for patients who satisfy the eligibility criteria described in Table 1. Some candidates were also identified by site clinical staff familiar with their medical history. Typically between 250 and 300 eligible patients are identified by searching the hospital records of the major community hospital in the region. Candidates are eligible to participate in the study if they meet all inclusion and none of the exclusion criteria listed in Table 1 and become participants on the signing of informed consent in the presence of an independent witness.

**Table 1 Tab1:** **Clinical criteria for eligibility**

Criteria	Type	Description
Age	Inclusion	50 years old and over at consent.
Cognitive capacity	Inclusion	Abbreviated Mental Test (AMT) [23] score >7.
Unplanned acute admissions	Inclusion	A rate of unplanned acute admission with the required principal diagnosis code(s) indicated below:
		a) ≥2 in the last 12 months, or
		b) ≥4 in the previous 5 years.
ICD-10-AM principal diagnosis code(s) for each unplanned acute admission	Inclusion	Code(s) for each unplanned acute admission indicate a diagnosis for one or more of the following chronic conditions:
		a) Chronic Obstructive Pulmonary Disease (J41 – J44, J47 and J20, with secondary diagnosis of J41-J44, J47),
		b) Coronary Artery Disease (I20 – I25),
		c) Hypertensive Diseases (I10 – I15, I11.9. Note: Hypertensive Heart Failure (I11.0) is included in Congestive Heart Failure),
		d) Congestive Heart Failure (I11.0, I50, J81),
		e) Diabetes (E10 - E14),
		f) Asthma (J45).
Unsuitable conditions	Exclusion	The study team considers the presence of the following conditions to be unsuitable for participation in the study:
		a) Any form of cancer,
		b) Any neuromuscular disease
		c) Any psychiatric conditions.
Care team	Inclusion	The eligible patients must be under the care of any of the following:
		a) General Practitioner
		b) Community Nurse
Care programs	Inclusion	Participation in one of the following government care programs:
		a) Commonwealth Chronic Disease Management
		b) Commonwealth Coordinated Veterans’ Care Program
		c) NSW Connected Care Program
Unsuitable care programs	Exclusion	Participation in one of the following government care programs:
		a) Commonwealth Extended Aged Care in the Home

For the purposes of our study unplanned admissions are all admissions other than:Admissions from the waiting list (including both the surgical list and the medical waiting list);Admissions listed as "regular same day planned admissions" which are admissions that are intended regular and planned same‒day admissions for an on‒going phase of treatment, such as renal dialysis or chemotherapy.

Following the signing of a consent form and completion of the Entry Questionnaire, Test patients are connected to the internet and supplied with the TMC Telemonitoring system and trained on its use by the Project Officer (PO) at each site. Their vital signs and questionnaire responses are subsequently monitored on a daily basis by the Clinical Care Coordinator (CCC). On site visits and technical support as well as the obtaining of Consent and the administration of Exit questionnaires are the responsibility of the PO.

Control patients also complete the Entry questionnaire but otherwise continue to receive normal care. For each intervention participant, as many as six control candidates are automatically case matched on gender, age, chronic condition and Socio-Economic Indexes for Areas (SEIFA) [24]. On their consent the two closest matching control candidates commence as participants in the study. The remaining four candidates are held in reserve. Table 2 below demonstrates the case matching process.

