**Table 3 Tab3:** **Key elements of the Entry and Exit Questionnaires**

Section	Source/questionnaire
1-3	CSIRO Standard Screening Medical Questionnaire [29] + additional trial specific questions
	Selected questions from Living with Diabetes Study [30]
	Selected questions from Fat and Fibre Barometer [31]
4	Active Australia [32]
5	Kessler 10 [33]
6	Dimensions from HeiQ (Living with and managing medical conditions) [34]
7	EuroQol EQ-5D [35]
8	Dimensions from HeiQ (Social Isolation) [34]
9	Morisky Medication Adherence [36]

Once each Test patient is consented, an automated case matching process is carried out as already described.

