**Schematic diagram of different data sources and their secure integration.**

 Entry and Exit Questionnaires are administered on line by PO’s when Test and Control patients are consented and are stored in OpenClinica Periodic Questionnaires (daily, weekly or monthly) are scheduled on the TMC clinician website and are presented and administered directly on the patient telemonitoring system. The results are stored in the TMC servers. Patient vital signs are recorded as longitudinal records and original waveforms are recorded and stored in the TMC server for quality control and diagnostic purposes. All records are accessible to the clinicians via the TMC clinician portal. Hospital Data is sourced from the Patient Administration Systems of hospitals servicing the trial sites and is supplied in the format of the Hospital Roundtable [28]. This comprehensive data set is requested for four years prior to enrolment and for the duration of the trial. MBS Data available from the Department of Human Services following Ethics Approval. This provides a comprehensive record of all primary care services provided under the national health insurance scheme PBS Data available from the Department of Human Services following Ethics Approval. This provides a comprehensive record of all medications dispensed under the national health insurance scheme. MBS and PBS Data is available for a total of 4.5 years prior to and including the duration of the trial. HIE Data from focus groups and structured interviews are transcribed and annotated before storage in OpenClinica.

Technical details on the data architecture designed to provide secure Role Based Access Control to de-identified patients data for research and analysis has been previously reported [27].

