### Questionnaire instruments

A number of questionnaire instruments were developed or adapted from the literature for use in the trial. All Patients enrolled in the study were required to take an Entry and Exit Questionnaire. This questionnaire instrument was developed from a base CSIRO CAFHS Human Research Ethics Standard Screening Medical Questionnaire [29] with the addition of other questionnaire instruments either wholly or in part, measuring demographic, lifestyle, health and disease characteristics. Key elements of the Entry and Exit Questionnaires are described in Table 3 below.

In addition to the Entry questionnaire, a number of questionnaires are scheduled and administered during the trial with varying frequency. These are described in Table 4 below.

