### Data analysis

Data will be analysed using a range of conventional statistical methods used in bio-statistics as well as model based methods more commonly found in the scientific statistical literature.

The independent samples t-test is commonly used when two separate sets of independent, randomly selected and normally distributed samples are available, one from each of the two populations being compared. However as explained previously, our project design makes random selection of Test and Control patients impossible and the alternative Before and After Control Intervention (BACI) design was adopted [22]. This design involved the site PO selecting the test patient first and then selecting from the remaining eligible test patients the controls that best match each test patient in turn.

As a consequence statistical comparisons in this study can only be validly made on Test – Control matched pairs and tested using the paired samples or repeated measures t-tests. We expect to obtain data from 125 test patients and up to 250 control patients. When two or more matched Control patients are available their data is averaged.

Data will be routinely tested for normality and if not normal, the appropriate transform, often log functions, will be applied to normalise the data prior to applying paired samples or repeated measures t-tests. Baseline characteristics will be described for time intervals as mean ± SDs for continuous symmetrical variables and means and 95% Confidence Intervals (CI) for skewed data. When before intervention data are available on outcomes, then the differences between the test and their controls will be tested to examine if there are any differences in the before intervention period. This process will be examined visually by examining boxplots of the time stamped differences (e.g., differences between the respective monthly variables eg. hospital costs) between test and control patient outcome measures.

As is common in the life sciences our data may be lognormal when not zero and may contain numerous zero values. In these circumstances the data will be modelled using a lognormal distribution for positive values, together with an additional probability mass at zero. This type of distribution is commonly referred to as delta-lognormal. 95% Confidence limits are calculated according to the method of Zou, Taleban and Huo [37].

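### The Project Officer who trains and supports Test patients also administers the Exit quality-of-life and distress scales, so a reporting shift confined to the Test group could be read as benefit

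*Protocol article*

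**What the plan says.** Under Selection of trial participants, Test patients complete the Entry questionnaire, are connected, and are then "trained on its use by the Project Officer (PO) at each site". The same paragraph gives the Project Officer the site visits and technical support, and adds that "the obtaining of Consent and the administration of Exit questionnaires are the responsibility of the PO". Daily review of vital signs and questionnaire responses belongs to a different role, the Clinical Care Coordinator.

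For the other group, "Control patients also complete the Entry questionnaire but otherwise continue to receive normal care". Controls do take the Exit form: under Questionnaire instruments, "All Patients enrolled in the study were required to take an Entry and Exit Questionnaire". The data-source list under Data architecture says that "Entry and Exit Questionnaires are administered on line by" the Project Officers, for Test and Control patients alike.

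Table 3 places Kessler 10, EQ-5D and heiQ dimensions in the Entry and Exit questionnaires. Aims and objectives lists, as the research question on patient outcomes, "Quality of life, progression of chronic condition, wellbeing, medication adherence".

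Table 4 also schedules EQ-5D weekly and Kessler 10 monthly. According to Data architecture, periodic questionnaires run on the telemonitoring system, which only Test patients are described as receiving.

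Data analysis sets a one-tailed matched-pair t-test at 0.05 for intervention effects and averages two Controls within a set.

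**The concern.** By Exit, a Test patient has been trained by the officer and could call on that officer for visits and technical help during an intervention of 6 to 18 months (Classical BACI designs and extensions). A Control is described as having met the officer for consent and Entry only. If the patient answers distress and quality-of-life items to that officer, or in the officer's sight, some Test patients may report themselves better than they are.

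The design does not remove such a shift. Entry comes before connection and training, so the working relationship does not exist at baseline and subtracting Entry values leaves the shift in place. Matching on age, gender, diagnosis and SEIFA does not bear on it. A change seen in one group only, and only after the start, is exactly what the before/after by Test/Control contrast estimates.

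For EQ-5D and Kessler 10 no other data rescue the comparison, because the readings taken on the device have no Control counterpart. At stake is whether a reported gain in quality of life or distress can be told apart from courtesy to the officer.

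**Working it through.** **Where the shift could enter**

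| Step | Test | Control |
|---|---|---|
| Entry questionnaire | officer-administered, before training | officer-administered |
| Training, visits, technical support | officer | none described |
| Exit questionnaire | officer-administered | officer-administered |

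The administrator is the same in both groups. What differs is the middle row, which falls between the two measurements.

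**Inputs**
- Matched sets: 5 sites × 25 = 125 Test and 5 × 50 = 250 Controls, total 375. This reproduces the head count under Selection of trial participants.
- Test: one-tailed matched-pair t-test, α = 0.05 (Data analysis). The direction is not spelled out; I take it as benefit.
- Alternative n: 30, the effective sample size under Power calculations. Table 6 applies it to cost and use outcomes and has no row for EQ-5D, Kessler 10 or heiQ, so it is used here only as a lower illustration.
- Reporting shift b, in SDs of the set-level difference in change: an assumption, because the article gives no figure. Range shown: 0.05 to 0.30.

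**Smallest significant difference**

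The threshold is t(0.95, n−1)/√n. It is 0.148 SD at n = 125, 0.166 at 100, 0.192 at 75 and 0.310 at 30.

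**Chance of declaring benefit when the true effect is zero**

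Normal approximation: Φ(b√n − 1.645), with √125 = 11.18.
- b = 0.10: Φ(1.118 − 1.645) = Φ(−0.527) = 0.30
- b = 0.15: Φ(1.677 − 1.645) = Φ(0.032) = 0.51
- b = 0.20: Φ(2.236 − 1.645) = Φ(0.591) = 0.72

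Noncentral t with n − 1 degrees of freedom:

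| b | n = 125 | n = 30 |
|---|---|---|
| 0 | 5.0% | 5.0% |
| 0.05 | 13.8% | 8.4% |
| 0.10 | 29.7% | 13.4% |
| 0.15 | 50.9% | 20.0% |
| 0.20 | 71.9% | 28.3% |
| 0.30 | 95.5% | 48.4% |

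**On the questionnaire's own SD scale**

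Assume an Entry-Exit correlation r of 0.5 to 0.7, m = 1 or 2 averaged Controls, and no Test-Control correlation. The SD of the set-level difference is √[2(1−r)(1+1/m)], which runs from 0.95 (r = 0.7, m = 2) to 1.41 (r = 0.5, m = 1). At n = 125 the threshold is then 0.14 to 0.21 questionnaire SDs, and a shift of 0.2 questionnaire SDs is declared a benefit 47% to 76% of the time.

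**Does a two-sided test cure it?** No. At n = 125 and b = 0.20 the false-benefit rate is still 60%.

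**The case against.** - **No interview is documented.** The forms are administered online, and patients are said to take or complete them. Private entry on a form that the officer merely sets up would fit those words. This stands, and it is why the point is conditional. Still, the article separates device-administered from officer-administered forms and does not say that the officer stays away from the answers.
- **The contact may be slight.** Daily monitoring is the Clinical Care Coordinator's task, and the frequency of the officer's visits is not given. This stands: a reader might infer months of close help from the person asking the questions, and the article does not support that.
- **Selection by the officer.** Under Data analysis, "This design involved the site PO selecting the test patient first". A reader might take this as a further source of courtesy at Exit. It adds nothing to that mechanism.
- **The scales have no stated analytic rank.** Table 5, on which nearly all quantitative analysis is said to rest, has no row for EQ-5D, Kessler 10 or heiQ, nor has Table 6. This stands and limits the reach of the point.
- **The percentages describe any bias of that size.** This also stands. They say nothing on how large the shift is, and 125 complete sets is the upper end.
- **Test patients know they have the equipment.** Some reporting bias is unavoidable in an unblinded trial, and self-completion will not remove that part. Who administers the items is nevertheless a free choice.

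**Conclusion.** The point holds in a limited form. The article gives one role both the support of Test patients and the administration of the Exit scales. It describes no comparable contact with Controls, and the design cannot subtract a shift that begins after Entry. If the officer conducts the questionnaire or sees the answers, a benefit on EQ-5D, Kessler 10 or heiQ could not be separated from a reporting shift. This would come on top of the bias that any unblinded trial carries.

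The size is illustrative only: about 30%, 51% and 72% false benefit at 125 sets, and about 13%, 20% and 28% at 30, for assumed shifts of 0.10, 0.15 and 0.20 SD. These figures rest on zero true effect, complete sets and the one-tailed test.

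Two stronger readings are not supported. The percentages are not an estimate of this trial's error rate, since no figure in the article supports the shift. Nor are the trial's utilisation results biased by this route: hospital, MBS and PBS outcomes come from administrative records.

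**What to change.** - Under Selection of trial participants and Data architecture, state that the EQ-5D, Kessler 10 and heiQ sections are self-completed by the patient in both groups, in the same mode at Entry and Exit. The Project Officer neither reads the items nor sees the answers, and only arranges completion. Changing the mode at Exit alone would be open to dispute, since Test patients will have practised self-completion on the device and Controls will not.
- For patients whose Entry form was already administered by the officer, record the Entry mode, and adjust for it or report results by it.
- Record whether help was needed and report it by group, as description or as a cautious sensitivity analysis. Do not use it as an exclusion rule, because needing help is a post-intervention variable that may differ between the groups.
- State with the results that patient-reported differences remain open to unblinded reporting bias.

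The cost is an instruction to sites and two extra data fields (mode and help), with no added staff. The downside is somewhat more missing items, and some older patients will need help.
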